### Severe Clinical DILI

- Dies of any cause
- Requires a transplant
- Complications associated with liver complications/failure such as: hepatic encephalopathy, hemorrhage, kidney failure, medical ventilation, circulatory dysfunction and infections.

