### Recovery Outcome

At the end of the follow-up (at 12 weeks), the patient’s recovery outcome will be classified into 3 categories:

[1] **Full recovery**: ALT<2xULN, total bilirubin<2xULN**;**

[2] **Partial recovery** [ALT>=2xULN or total bilirubin>=2xULN, without increase in total bilirubin between D0 and W12] and patients without decrease in total bilirubin but in whom physicians considered that the decrease in ALT (**adaptive response**) allowed re-treatment of live-threatening disease such as non-liver cancer; If a patient has a re-treatment with severe complications as defined in [3] he will be classified as [3].

[3] **No recovery** including **severe complications** [biological severity (increase of total bilirubin between D0 and W12) or clinical severity (morbidity and mortality)].

Rules for dealing with data issues will be clarified in the statistical analysis plan (SAP). For example, if a patient dies from any cause (even if not directly associated with DILI) or is withdrawn/discontinues from the study, the patient’s data will be excluded from the Main Analysis Set but will be classified as per the last available measurement for the purposes of the Full Analysis Set.

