### Secondary Objectives

The new biomarkers will be compared to ALT and total bilirubin, which are the "Standard of Diagnosis" (including Hy's Law), and to ActiTest which is already commercially available for the secondary objectives:

- - - Investigate the performance of investigational biomarkers from baseline D0 to Week 12) to predict:

1. A subsequent increase in total serum bilirubin of at least 10 umol/l more than the baseline value (D0) or an elevation of total bilirubin to 34 umol/l (Hy's law is TBILI 2xULN together with ALT 3xULN) at any other measurements between D1 to W12;
2. Death or severe liver complications (including transplant and complications associated with liver failure such as: hepatic encephalopathy, hemorrhage, associated liver failure complications: kidney failure, medical ventilation, circulatory dysfunction and infections.
3. Type of liver injury (hepatic, cholestatic and mixed).
4. Time to discharge from hospital.
   - - For each of the outcomes in (i) to (iii) determine the best investigational biomarker with associated thresholds.
     - For each of the outcomes in (i) to (iii) determine the best combination of biomarkers with associated threshold.
     - Type of drugs suspected in DILI will be assessed.
     - The prevalence of associated liver risk factors such as alcohol consumption, metabolic factors, history of familial liver disease, history of drug adverse events, history of recreational drugs (cocaine, ecstasy, amphetamines), combination of different drugs and herbals will be assessed and may be incorporated into statistical models.

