### Methods

Proper risk assessment and signal detection as early as possible in clinical drug development are crucial to identify any potential of a drug to cause idiosyncratic liver toxicity. Given the time frame of five years for the SAFE-T consortium to achieve adequate qualification of selected liver biomarkers, it is highly unlikely that sample sizes required will be obtained when using Hy’s law only as signal definition.

For cholestatic liver injury cases, cut-off level for alkaline phosphatase will be 2 x ULN [3].

*Causality assessment:* Cases with suspected DILI should be initially ascertained by clinical judgement of the physician in charge and, subsequently, by the evaluation of an adjudication committee based on the following criteria: 1) an appropriate temporal relationship between the intake of the drug and the onset of the event, 2) the improvement of liver damage following the withdrawal of the drug if no fulminant or chronic liver failure is diagnosed, 3) exclusion of other causes of liver disease, 4) relapse following re-exposure when applicable and decided by clinicians in charge (as in chemotherapy cycles), and 5) previous reports of the adverse reaction. Cases will be further evaluated for causality assessment, by application of the Council for International Organizations of Medical Science (CIOMS)/Roussel Uclaf Causality Assessment Method (RUCAM) scale.

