### Secondary Endpoints: Time to Events

The time from D0 to reaching the following outcomes will be calculated:

1. Full Recovery from DILI;
2. Severe biochemical DILI
3. Severe clinical DILI (i.e. death or liver complications/failure).

Where a patient does not meet the criteria of the outcome, a censored time will be used as the time of last follow-up visit.

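### Severe clinical DILI counts death from any cause, while section 1.6.1 removes everyone who dies from the Main Analysis Set and no analysis set is named for the endpoint

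*Protocol*

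**What the plan says.** Section 6.3.2 (Severe Clinical DILI) lists three criteria. The first is "Dies of any cause", the second is transplant, and the third is a set of complications that count only in association with liver complications or failure. Section 2.2, item (ii), gives the matching objective as "Death or severe liver complications (including transplant and complications associated with liver failure such as" followed by examples, and does not restrict the cause of death. Section 6.4 repeats the endpoint as a time to event: "Severe clinical DILI (i.e. death or liver complications/failure".

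Section 7.1 applies ROC analysis to each binary outcome. Section 7.5 models each time-to-event endpoint with biomarkers as time-dependent covariates.

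The protocol foresees patients with serious non-liver disease. Section 1.6.1 speaks of a decrease in ALT that "allowed re-treatment of live-threatening disease such as non-liver cancer", and the causality criteria in section 3.6 include "relapse following re-exposure when applicable and decided by clinicians in charge (as in chemotherapy cycles". Among malignancies, section 3.4 names only liver metastasis as an exclusion.

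Section 1.6.1 also gives an example of a data rule that the SAP will clarify. A patient who "dies from any cause (even if not directly associated with DILI" leaves the Main Analysis Set and, in the Full Analysis Set, is classified by the latest measurement on file. Section 5.1 defines the Main Analysis Set by adjudicated inclusion criteria less the special groups, and does not mention deaths.

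**The concern.** The endpoint is labelled as severity of DILI, and the study asks whether new liver markers improve on ALT and total bilirubin in predicting the outcome of DILI. Section 6.3.2 applies two standards of attribution in one list: a complication must be connected to the liver, a death need not be. A patient whose liver tests have normalised and who then dies of cancer within the 12 weeks meets the definition.

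A liver-specific marker has no reason to foresee such a death. Where these deaths are counted, they lower its apparent performance and shrink its lead over the standard markers. A marker of general frailty could instead appear to predict DILI severity.

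The rule in section 1.6.1 creates the opposite problem. If it governs this endpoint, fatal DILI, the most severe outcome, disappears from the Main Analysis Set. The reader cannot tell which of the two applies.

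**Working it through.** **The passages side by side.**

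- Under section 6.3.2 alone, every death is an event, whatever its cause.
- Under section 1.6.1, no patient who dies is in the Main Analysis Set, so the death criterion of section 6.3.2 can never be met there. In the Full Analysis Set, classification by the latest measurement would rest on laboratory values, whereas section 6.3.2 would make the patient an event.
- Under section 5.1, patients who die stay in the Main Analysis Set if they met the adjudicated inclusion criteria.
- No section assigns an analysis set to severe clinical DILI.

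The rule is awkward even within section 1.6.1, because that section places mortality in its third recovery category.

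**Size of the dilution where deaths are kept.** The protocol gives no event rate, target AUROC or power for this endpoint, so there is no stated figure to reproduce. The only inputs from the document are 500 patients and 12 weeks of follow-up (section 3.1). The rest is assumed.

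Let A be the AUROC for liver-related events and f the share of events that are unrelated deaths. Assume that the marker does not separate unrelated deaths from non-events (AUROC 0.50). AUROC is linear in the case mix, so

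observed AUROC = (1 − f) × A + f × 0.50.

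With A = 0.80:

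- f = 10%: 0.72 + 0.05 = 0.77
- f = 20%: 0.64 + 0.10 = 0.74
- f = 30%: 0.56 + 0.15 = 0.71
- f = 50%: 0.40 + 0.25 = 0.65

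If both markers are uninformative about unrelated deaths, a true gap of 0.10 between a new and a standard marker becomes (1 − f) × 0.10. That is 0.09, 0.08, 0.07 and 0.05 at the same values of f.

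**What f might be**, for assumed counts among 500 patients:

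| Liver-related events | Unrelated deaths | f | 0.80 reads as |
|---|---|---|---|
| 25 (5%) | 5 (1%) | 5/30 = 17% | 0.75 |
| 25 | 10 (2%) | 10/35 = 29% | 0.71 |
| 25 | 25 (5%) | 25/50 = 50% | 0.65 |
| 50 (10%) | 5 | 5/55 = 9% | 0.77 |
| 50 | 10 | 10/60 = 17% | 0.75 |
| 50 | 25 | 25/75 = 33% | 0.70 |

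**Against sampling error.** By the Hanley-McNeil variance, the half-width of the 95% confidence interval at AUROC 0.80 is about 0.11 with 25 events and 0.08 with 50. A loss of 0.03 (f = 10%) lies well inside that; a loss of 0.09 (f = 30%) is of similar size. Unlike sampling error, the loss does not shrink with more patients.

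**Time to event.** The direction is the same for a liver-specific marker, because the composite hazard mixes a component that the marker tracks with one that it does not. No figure is offered, as nothing in the protocol supports one.

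**The case against.** A reader might infer that every unrelated death is certain to count as a DILI event in both the ROC and the time-to-event analyses. The protocol does not support that. The sentence in section 1.6.1 that foresees unrelated deaths goes on to remove those patients from the Main Analysis Set and to classify them by the latest measurement in the Full Analysis Set. If that rule governs this endpoint, no dilution arises in the Main Analysis Set. It does not cure section 6.3.2, however: it stands in the recovery-outcome section as an example for the SAP, section 5.1 omits it, and it would also discard DILI deaths.

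A reader might also infer that every marker is pulled toward no effect. That is too broad. The dilution concerns liver-specific markers; a marker of general frailty may gain.

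All-cause death is a defensible component. It is objective and avoids attributing deaths in a disease whose causality is itself a judgement. This stands, and is a reason to keep the all-cause version rather than replace it.

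Coding unrelated deaths as non-events in the ROC has its own fault: a patient who dies early, before the liver course is known, would be labelled free of severe DILI. This stands too.

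Finally, the endpoint is secondary, and details of competing events usually belong to the SAP. But the endpoint definition, and its conflict with the rule on deaths, are fixed in the protocol.

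**Conclusion.** The point holds in limited form. Severe clinical DILI includes deaths of any cause in a cohort where unrelated deaths are foreseen, so in any set that keeps deaths it mixes liver severity with other mortality. Section 1.6.1 would instead empty the death component in the Main Analysis Set, and no analysis set is named. As written, either unrelated deaths count as DILI events or no deaths count, and neither measures fatal DILI.

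The size cannot be determined from the protocol. The fall from 0.80 to between 0.77 and 0.71 rests on an assumed 10% to 30% share of unrelated deaths and on a marker uninformative about them. A share of 50% is arithmetic only; nothing in the document makes it likely within 12 weeks. The primary endpoint, full recovery at week 12, is not the subject of this point.

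**What to change.** - Reconcile sections 1.6.1, 5.1 and 6.3.2 so that patients who die stay in the analysis of severe clinical DILI, and name the analysis set for this endpoint.
- In sections 2.2(ii), 6.3.2 and 6.4, define two versions: one with all-cause death, and one with death judged liver- or DILI-related by the existing Adjudication Committee, blind to the investigational biomarker results.
- In the liver-related version, treat other deaths as a competing event in the time-to-event analysis. In the ROC analysis, show results with those patients excluded and with them counted as non-events, so that the effect of the choice is visible.

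The cost is amendment wording and a cause-of-death item for the committee. That is a small new task, since its stated role is to confirm DILI and inclusion. Attribution of deaths needs judgement; reporting the all-cause version alongside covers that weakness.

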### Drug-Induced Liver Injury

Many drugs can unexpectedly induce injury to the human liver. These kinds of side effects can be life-threatening and may lead to withdrawal of the drug treatment.

Drug-induced liver injury (DILI) may occur in a dose-dependent way, as is the case for acetaminophen, or as an idiosyncratic reaction and may present as acute liver failure. Acute DILI is a rare event (14 per 100,000) but its unpredictable nature and the possible fatal course make it a major health concern. DILI has been and still is one of the most concerning safety issues in both drug development and during the routine use of therapeutic drugs. DILI has been the most frequent single cause of safety-related drug marketing withdrawals for the past 50 years (e.g., iproniazid), continuing to the present (e.g., ticrynafen, benoxaprofen, bromfenac, troglitazone, nefazodone). Hepatotoxicity discovered after marketing approval has also limited the use of many drugs, including isoniazid, labetalol, trovafloxacin, tolcapone, and felbamate [2]. As of yet, there are limited possibilities to detect or monitor such liver injury.

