### Definition of Baseline measurement (D0)

Day 0 (D0) is the first day of admission into this study when the informed consent is signed. D0 serum sample will be stored in the SAFE-T Biobank. This Baseline measurement may be performed the first day of hospitalization for DILI but could also be the First-on-drug measurement on drug.

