### Secondary Endpoints: Binary Outcomes

A series of binary outcome variables will be defined by an indicator set to one if the following criteria are met and zero otherwise.

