### Severe Biochemical DILI

A patient will be deemed to have “severe biochemical DILI” if the patient has:

- An increase in total serum bilirubin of at least 10 umol/l more than the baseline value (D0); or
- An elevation of total bilirubin to 34 umol/l (Hy's law) at any other measurements between D1 to W12;

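### The complications item of severe clinical DILI has no post-baseline condition, so complications already present at D0 can count as predicted events

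*Protocol*

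**What the plan says.** Section 6.3 gives the coding rule for all binary secondary endpoints: "A series of binary outcome variables will be defined by an indicator set to one if the following criteria are met and zero otherwise". Section 6.3.2 then lists death of any cause, transplant, and a third item: "Complications associated with liver complications/failure such as: hepatic encephalopathy, hemorrhage, kidney failure, medical ventilation, circulatory dysfunction and infections". None of the three carries a time condition. Only the third can realistically be met before follow-up begins.

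The matching objective, 2.2(ii), is also untimed: "Death or severe liver complications (including transplant and complications associated with liver failure such as: hepatic encephalopathy", followed by the rest of the list. Section 6.4 makes severe clinical DILI the third time-to-event outcome and fixes the origin: "The time from D0 to reaching the following outcomes will be calculated". Its only handling rule is censoring at the last visit for patients who never meet the criteria.

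On who may be enrolled, section 1.7.3 says of D0: "This Baseline measurement may be performed the first day of hospitalization for DILI". Section 1.4 says that DILI can occur "as an idiosyncratic reaction and may present as acute liver failure". Section 3.2 lets the qualifying laboratory value be up to 4 weeks old at baseline. Section 3.4 excludes alternative causes of liver injury, not complications of DILI.

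**The concern.** A marker can predict only what has not yet happened. If a patient already has kidney failure associated with liver failure when the D0 sample is drawn, an abnormal D0 value shows that the marker recognises a complication in progress. It does not show that the marker foresees one. Sections 2.2 and 7.1 describe the task as prediction, but the indicator in section 6.3.2 does not separate the two cases.

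At stake are the AUROCs for this endpoint, and the best marker, best combination and thresholds that section 2.2 asks for on outcome (ii). Cross-validation does not help: it guards against overfitting, whereas here the same outcome definition applies in every fold. The time-to-event analysis has its own gap. A patient who meets the criteria at the origin is neither censored under section 6.4 nor given an event time, so the binary and survival analyses may end up counting different events.

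**Working it through.** **1. Does any other part of the protocol supply the missing condition?**

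| Place | Post-baseline condition |
|---|---|
| 2.2(i), bilirubin rise | Yes: "A subsequent increase in total serum bilirubin of at least 10 umol/l more than the baseline value (D0") |
| 2.2(i) and 6.3.1, 34 umol/l alternative | A measurement window: "at any other measurements between D1 to W12" |
| 2.2(ii), clinical outcome | None |
| 6.3 and 6.3.2, indicator and complications item | None |
| 6.4, third outcome | Origin at D0; no rule for patients who meet the criteria at D0 |
| 1.6.1, clinical severity in category [3] | None |

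The biochemical outcome is tied to later measurements and the clinical outcome is not.

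**2. Can affected patients be enrolled?** Sections 1.4, 1.7.3, 3.2 and 3.4 together leave this open. The requirement in section 3.2 that the patient can give written consent limits entry with marked encephalopathy or on ventilation. It does not keep out kidney failure, hemorrhage or infection associated with liver failure.

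**3. How much could it matter?** The protocol states no event rate, AUROC or prevalent share, so there is no figure to reproduce. Every value of q and every AUROC below is an assumption.

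Let q be the share of scored events already present at D0. The AUROC is the probability that a case has a higher value than a non-case. With a common non-event group it is therefore exactly linear in the case mix:

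AUROC (as scored) = (1 − q) × AUROC (incident) + q × AUROC (prevalent)

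Inflation = q × [AUROC (prevalent) − AUROC (incident)]

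A simulation at q = 25% with 0.70 and 0.90 gave 0.7497 against 0.750 from the formula.

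| Incident / prevalent AUROC | q = 5% | q = 10% | q = 25% | q = 50% |
|---|---|---|---|---|
| 0.70 / 0.90 | 0.710 | 0.720 | 0.750 | 0.800 |
| 0.70 / 0.80 | 0.705 | 0.710 | 0.725 | 0.750 |
| 0.60 / 0.80 | 0.610 | 0.620 | 0.650 | 0.700 |
| 0.60 / 0.90 | 0.615 | 0.630 | 0.675 | 0.750 |

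For 0.70 / 0.90 the inflation is 0.05 × 0.20 = 0.01 at q = 5% and 0.50 × 0.20 = 0.10 at q = 50%. Over the whole table it runs from 0.05 × 0.10 = 0.005 to 0.50 × 0.30 = 0.15.

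**4. What does removing prevalent events cost in precision?** Take the planned 500 patients (section 3.1), an assumed 5% or 15% with an event, an AUROC of A = 0.70, and the Hanley–McNeil variance with n1 events and n0 non-events:

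SE² = [A(1 − A) + (n1 − 1)(U − A²) + (n0 − 1)(V − A²)] / (n1 × n0), where U = A/(2 − A) and V = 2A²/(1 + A).

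- 5% with events: 25 events and 475 non-events give a 95% half-width of 0.117. With q = 25%, 25 × 0.75 = 18.75 events remain, and the half-width is 0.135.
- 15% with events: 75 events and 425 non-events give 0.070. With q = 25%, 75 × 0.75 = 56.25 events remain, and the half-width is 0.080.

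**The case against.** The best defence is that the intent is plain. Sections 2.2 and 7.1 speak of prediction, section 6.4 counts time from D0 to reaching the outcome, and sections 1.6.1, 7, 7.1 and 7.5 leave data rules and analysis details to the SAP. The point about intent stands, but intent does not tell a programmer how to code a patient with a complication at D0. Here the protocol itself fixes the endpoint definition.

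Several stronger readings are tempting and are not supported:

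- *Such patients are scored at time zero.* A reader might infer this from the D0 origin. The protocol does not say so; it simply has no rule for them.
- *Any kidney failure, hemorrhage or infection at entry counts.* Section 6.3.2 ties the complication to liver complications or failure.
- *The biochemical endpoint requires new onset throughout.* It does not. The bilirubin rise and the 34 umol/l level are alternatives. The D1 to W12 phrase is a measurement window on the second, which a patient already above 34 umol/l at D0 can meet on D1.
- *Prevalent complications will certainly be common.* Section 1.4 is general background and section 1.7.3 says only what may happen. The share could be small.
- *The new markers are favoured over the standard ones.* Prevalent severe cases may also raise the AUROCs of ALT and bilirubin. Bias in the difference is not shown in either direction.

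**Conclusion.** The point holds for the complications item of severe clinical DILI, and for that item only. As written, the rule admits complications already present at D0 into an outcome meant to be predicted, and the time-to-event analysis has no handling for those patients. Absolute AUROCs and thresholds for this endpoint would be too favourable wherever markers separate prevalent cases better than incident ones.

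The size is unknown. It depends on the prevalent share and on two AUROCs that the protocol does not give. Inflation of 0.01 (q = 5%) to 0.10 (q = 50%) at 0.70 / 0.90 is illustration only, and it assumes a common non-event group. The effect on the comparison with ALT and bilirubin has no known direction. Because the endpoint is secondary, this should be corrected but does not threaten the primary analysis of full recovery at W12.

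**What to change.** 1. In sections 6.3.2, 6.4 and 2.2(ii), count a listed complication only if it is first present after the D0 sample and up to W12. Leave death and transplant as they are.
2. For patients with a listed complication at D0, choose one rule in advance: either count only death, transplant or a new type of complication, or remove them from the risk set for this endpoint. The choice matters. Under the first rule, those without a new event join the non-event group, and the formula above no longer describes the change. Under either rule, report them separately as severe at presentation.
3. Where samples after D0 serve as predictors, use only those taken before the event. An onset condition at D0 does not by itself prevent later samples from coinciding with or following the complication.
4. Confirm that the case report form captures complication status at D0 and onset thereafter. The data collection list in section 3.6.3 records current medical conditions and the date of symptom onset at each time-point, but does not clearly record onset dates of complications.
5. Align the clinical severity part of category [3] in section 1.6.1.

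The cost is a wording change, possibly one added data field, and fewer events. In the illustration with q = 25%, the 95% half-width grows from 0.117 to 0.135 with 25 events at the outset, and from 0.070 to 0.080 with 75.
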